### Withdrawal of the study participants

Participants may withdraw from the study at any time without giving a reason. However, the data which has been collected will be kept up to the point of withdrawal. A participant will be withdrawn if they are lost to follow-up or request to leave the study or have premature delivery before 36 weeks gestation. If the participants in the supervised training group do not attend the face-to-face sessions without a reason, they will be considered as withdrawn.

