### Sample size

As this is a feasibility study, formal sample size calculation has not been performed. The sample size for a feasibility study needs to meet a balance between not being too large, which may cause a burden on health professionals and participants, and also not being too small as the consent rate, attrition and sample size for a large-scale RCT need to be calculated. Based on the recommendation from the National Institute for Health Research [25], an overall sample size of 30 or greater was considered sufficient for a feasibility study. In addition, a sample size between 24 and 50 is sufficient to calculate a standard deviation of an outcome, which can then be used for a formal calculation for a full-scale RCT [26, 27]. A study by Whitehead et al. [28] developed a method for determining the best approach to calculate the required sample size for a pilot trial and found that for studies where standardized differences are large, to achieve 90% power in the main trial, the required sample size for each arm is 10. For women receiving nonsurgical therapies for incontinence, reductions of four to six points in the International Consultation on Incontinence Questionnaire-Urinary Incontinence Short Form (ICIQ-UI SF) are needed to show clinically meaningful [29]. Two further studies consider the attrition rates in group-based pelvic floor muscle training in pregnant women or postpartum women range from 8.57 to 53.33% [30, 31]. Therefore, this study aims to include a sample size of 48 participants with 24 in each arm.

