All the group-based training sessions in the programme will be provided by one midwife to ensure consistency. The midwife will be trained beforehand by the principal researcher about the PFMT programme. The participants will be required to meet the midwife for group supervision once a month on the day of their regular antenatal check for consecutive four consecutive months (approximately 24 gestational weeks, 28 gestational weeks, 32 gestational weeks and 36 gestational weeks). The group supervision sessions will last for about 45 min which include attendance registration and progress review (5 min), education on the causes of UI and PFMT (10 min), skills training in sitting and standing positions (20 min), discussion on what is taught (8 min) and reminder about the next session (2 min). The registration of attendance and the training diary which will be provided to the participants after each session will be monitored to record adherence to the programme. Women who attend at least 75% of the supervision sessions will be considered as adherent. Motivation to maintain PFMT will be emphasized by the midwife and supported by WeChat groups which will be limited to the eight pregnant women in the group session. A reminder to practise PFMT as well as the audio instructions on doing PFMT will be sent automatically in the WeChat group twice a day. In addition, leaflets on PFMT, training diaries and stickers which motivate the participants to undertake PFMT will be provided. The PFMT leaflets and training diary were provided as Additional file 3. One day before the next session, a reminder of the session date will be sent to the WeChat group. The participants will be encouraged to discuss any topics related to PFMT and UI in the WeChat group to facilitate peer support. The midwife and the principal researcher will adopt administrative roles and monitor the WeChat groups but will not answer questions or participate in discussions. Any problems which the pregnant women encountered during the exercises will be addressed during face-to-face supervision. There will be ground rules set for the groups, for example, the women in the groups need to keep the information confidential within the group and treat each woman in the group with respect. If any women break the ground rules or discuss information in the WeChat group that is unsafe, the principal researcher will remind the women about the ground rules and correct any information that is dangerous. During the development of this study, the barriers identified from the systematic review [13], survey [24] and discussion with stakeholders, such as time commitment, forget to continue PFMT were mapped to the COM-B model and explored in a separate study. For reasons of equipoise, women in the comparator group will be offered the group-based PFMT intervention at the end of the study if they wish.

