### Measures

The outcomes will involve both qualitative and quantitative outcome measures. One focus group interview with the participants and one semi-structured interview with the midwife who delivered the intervention will be held by the principal researcher in an office in the antenatal clinic. The midwife will not be involved in the focus group interview with the participants. The focus group interview aims to assess the acceptability of randomization, the outcome measure and the intervention. About six to eight participants will be purposively sampled from the intervention groups which means the participants were selected based on the researcher’s own judgement. The principal researcher aimed to select participants including both women who strongly adhered to the training programme and women who did not attend at least three face-to-face sessions. Compared to the other sampling approach, purposive sampling can better match the sample to the aims and objectives of the research [35]; however, it may bring a source of bias into the research which needs to be discussed in the interpretation of the interview when the feasibility study is written up [36]. The participants will be asked to discuss their experience and acceptability of the randomization process, the group-based PFMT, the UI outcome measure which is proposed for use in the future trial and their suggestions for future PFMT interventions. Discussion between participants will be encouraged. The consent for the interview will be obtained along with the consent for participating in the programme.

The semi-structured interview with the midwife aims to assess the acceptability of delivering the intervention. The midwife will be asked to discuss her experience of delivering the intervention, challenges and views of the feasibility of implementing the group-based PFMT across a larger population in Nanjing city. The interview will be conducted by the principal researcher in one office in the antenatal clinic. Both interviews will be digitally audio-recorded and transcribed verbatim.

The quantitative outcome measure will be recruitment rates and retention of participants, as well as the completion rates of UI outcome measures. The detail of outcome measures is shown in Table 1.

**Table 1 Tab1:** Details of evaluation measures

Outcome measures	Evaluation measures
Recruitment and eligibility	Number of participants recruited
	Percentage of eligible participants

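### The withdrawal rule counts unexplained non-attendance in the supervised arm as attrition, merging two feasibility outcomes that the protocol measures separately

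*Protocol article*

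**What the plan says.** Three sentences under Withdrawal of the study participants matter here.

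- Non-attendance: "If the participants in the supervised training group do not attend the face-to-face sessions without a reason, they will be considered as withdrawn". No number of missed sessions is given, and the control arm has no counterpart.
- Other grounds, in either arm: "A participant will be withdrawn if they are lost to follow-up or request to leave the study or have premature delivery before 36 weeks gestation".
- Data: "However, the data which has been collected will be kept up to the point of withdrawal". Nothing is said about collecting data afterwards.

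Other sections treat attendance as something to be measured:

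- Aims and objectives lists recruitment and retention as one objective, and attendance and adherence as another.
- Interventions sets the adherence cut-off: "Women who attend at least 75% of the supervision sessions will be considered as adherent". There are four sessions, so this means three.
- Table 1 has separate rows for dropout and for sessions attended, and also asks why attendance was poor.
- Measures wants the focus group to include "women who did not attend at least three face-to-face sessions".
- The progression criteria, in the text after Fig. 2, set retention at 40/48, 38/48 and 36/48 questionnaires submitted (baseline, first and second follow-up). Attendance is set separately at 18/24 women completing at least three of four sessions.

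**The concern.** A woman who stops coming to sessions without explanation has not adhered. Whether she would still fill in a short questionnaire is a different question, and a feasibility study needs both answers. The withdrawal rule gives one behaviour both labels. Recorded attrition then partly reflects the rule rather than women's willingness to stay in follow-up, and it does so in one arm only.

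Three things are at stake. First, the retention criteria feed the decision to proceed, and a pooled retention figure would not show an imbalance created by the rule. Second, Analysis of quantitative data and qualitative data says the group comparison serves to obtain standard deviations and plan the definitive trial's sample size. If withdrawn women return no later questionnaires, the supervised arm's follow-up data under-represent non-attenders. Third, the rule sits uneasily with the wish to interview low attenders and record why attendance was poor, since the women it removes are those whose reasons are not yet known.

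The preterm-delivery rule is a separate and smaller matter. It applies to both arms. Its cost is the assessment 42 days after delivery, which a woman delivering before 36 weeks could still complete.

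**Working it through.** **Inputs from the protocol.** 48 women, 24 per arm (Sample size); four sessions, adherent at three or more (Interventions); progression thresholds (Measures); cited attrition of 8.57% to 53.33% in comparable programmes (Sample size).

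**Stated thresholds.** 40/48 = 83.3%, 38/48 = 79.2%, 36/48 = 75.0%, 18/24 = 75.0%, 3/4 = 75%. All agree with the protocol's rounded figures.

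**Losses the criteria allow.**
- Attendance: 24 − 18 = 6 women may fall below three sessions.
- First follow-up: 48 − 38 = 10 losses.
- Second follow-up: 48 − 36 = 12 losses.

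**Effect of the rule with no other loss.** Let k be the number of supervised-arm women withdrawn for unexplained non-attendance. Supervised-arm retention is (24 − k)/24, control retention is 24/24, and pooled retention is (48 − k)/48.

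| k | Supervised arm | Control | Pooled |
|---|---|---|---|
| 0 | 24/24 (100%) | 24/24 (100%) | 48/48 (100%) |
| 2 | 22/24 (91.7%) | 24/24 (100%) | 46/48 (95.8%) |
| 4 | 20/24 (83.3%) | 24/24 (100%) | 44/48 (91.7%) |
| 6 | 18/24 (75.0%) | 24/24 (100%) | 42/48 (87.5%) |

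At k = 6 the pooled figure still passes both follow-up criteria, despite a 25-point difference between arms. The rule alone fails the first follow-up criterion only from k = 11 (37/48) and the second only from k = 13 (35/48).

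**Effect with ordinary loss added.** Suppose each woman not withdrawn by the rule is lost independently with probability d. The number submitting is X ~ Binomial(48 − k, 1 − d), and the chance of meeting each criterion is P(X ≥ 38) or P(X ≥ 36). The 8.57% is the lower end of the protocol's cited range; 15% and 20% are assumptions.

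| d | Criterion | k = 0 | k = 3 | k = 6 |
|---|---|---|---|---|
| 8.57% | 38/48 | 0.998 | 0.964 | 0.710 |
| 8.57% | 36/48 | 1.000 | 0.996 | 0.936 |
| 15% | 38/48 | 0.904 | 0.639 | 0.225 |
| 15% | 36/48 | 0.978 | 0.873 | 0.555 |
| 20% | 38/48 | 0.639 | 0.297 | 0.058 |
| 20% | 36/48 | 0.852 | 0.588 | 0.238 |

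The k = 0 column assumes that non-attenders, if asked, would return questionnaires as often as other women. If they would return fewer, the part due to the rule is smaller than the gap between columns. The k = 6 column assumes that all six are withdrawn before the first follow-up at about 36 weeks.

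**The case against.** The strongest reply is that the sentence is merely loose. Missing the sessions can be read as never coming or stopping altogether, in which case a woman attending one or two of four would not trigger it. Women who give a reason are not withdrawn at all. Retention is counted by questionnaires submitted, and the protocol does not say that a later questionnaire from a withdrawn woman would be refused; the sentence on keeping data directly follows the one on voluntary withdrawal. Even at six withdrawals with no other loss, retention passes.

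Much of this stands, and it limits the size. The number affected while attendance is still met runs from 0 to 6, and six is the upper end. Stopping follow-up is the natural reading of withdrawal, but it is not stated. What does not fall away is that the rule gives non-attendance a second label in one arm only, with no defined trigger.

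A reader might infer more than the text supports:

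- *That randomised women are excluded from the analysis.* No section says so. Data up to withdrawal are kept, and the analysis set may be defined in an analysis plan. What follows from the text is loss of later data.
- *That withdrawn women leave the adherence denominator, so that 18/24 would be reported as 18/18.* The progression criteria write the denominators as 24 and 48.
- *That women who explain poor attendance are dropped.* The rule covers only those absent without a reason; the others remain available for interview.
- *That the preterm rule adds to one-sided attrition.* It applies to both arms, and the eligibility criteria already exclude women at high risk of preterm labour.

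**Conclusion.** The point holds and should be fixed, although it does not invalidate the study. As written, the rule turns unexplained non-attendance into attrition in the supervised arm only, while the objectives, the adherence definition, Table 1 and the progression criteria keep the two apart.

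In the upper case compatible with meeting the attendance criterion, six women are withdrawn. Supervised-arm retention is then at most 75% against up to 100% in controls, and 6 of 10 and 6 of 12 permitted losses are used. This assumes that all six absences are unexplained, that fewer than three sessions is enough to trigger the rule, and that withdrawal ends questionnaire collection. If only total non-attendance counts, the effect is smaller. Combined with ordinary loss, a trial that meets its attendance criterion could miss a retention criterion partly because of the label.

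The follow-up UI data and standard deviation passed to the definitive trial would under-represent non-attenders. The size of that effect cannot be given, because the protocol has no UI figures by attendance. The preterm rule needlessly gives up the 42-day questionnaire in both arms; the number of women concerned is not stated.

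**What to change.** 1. Distinguish stopping session attendance from withdrawal from the study, and delete non-attendance as a ground for study withdrawal.
2. Count a woman who misses sessions, explained or not, as attending the number she attended, with all 24 supervised-arm women in the denominator. Record the reason where she gives one.
3. Request each remaining questionnaire from all randomised women, including non-attenders and those delivering before 36 weeks, unless they withdraw consent.
4. Report retention at each follow-up by arm as randomised, beside the pooled figure used for progression.

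The cost is protocol wording and a few additional questionnaires of 5–10 minutes each. Sample size, sessions and progression thresholds are unchanged.

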### Adverse events report

Although there is no report on the adverse events of PFMT, any adverse events or unintended effects of trial interventions will be collected and reported to the principal researcher and the Research Ethics Committee.

### Data analysis

#### Process evaluation

The process evaluation will be conducted based on the logic model (Fig. 3) for the intervention that was developed with stakeholders. The logic model will be used to monitor intervention fidelity and provide insight into how the intervention did or did not work in practice, identify any unintended consequences and refine the design of the future trial. It is useful for evaluation because it can help to optimize and structure data collection and analysis to explore the main aspects of an intervention and relationships between them [40]. The logic model can be used, for example, to evaluate the questions based on the programme, the information to answer the questions, the time of the collecting data and the data collection methods [41].

**Fig. 3 Fig3:**
[figure not shown]
Logic model of the group-based PFMT programme

#### Analysis of quantitative data and qualitative data

Outcomes of the number and proportion of pregnant women who are screened and then eligible for the study, the number and proportion of pregnant women who consent to participate in the programme and be randomized to different groups and the number and proportion of pregnant women who completed outcome measures will be analysed using descriptive statistics. Group comparisons in UI outcome measures will be analysed using the Mann–Whitney test and chi-square test and presented with confidence intervals to evaluate evidence of the promise of the intervention. As this is a feasibility study, the analysis between groups is conducted only to obtain standard deviations of quantitative outcome measures of UI and to estimate sample size for the definitive RCT rather than aiming to show a definitive difference between the group-based PFMT group and the control group.

Qualitative data from the interviews will be analysed using pragmatic thematic analysis [42] to explore an in-depth understanding of the proposed programme, i.e. what are the experiences of participating in the intervention that may affect the feasibility of the intervention and future trial design. Thematic analysis allows potential themes from the transcripts to be identified without trying to fit the transcripts into one pre-existing coding frame. Therefore, this method is applied in many qualitative studies and is considered to be accessible and data-driven [42].

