### Interventions

The participants in the intervention group will receive PFMT supervision in groups of eight women. The intervention will include verbal instruction on PFMT, the use of models and pictures of the pelvic floor to help women identify their pelvic floor muscles and then guide them on how to contract the pelvic floor muscles correctly. The content of this PFMT programme was adapted from a published protocol [34] and co-designed with stakeholders to suit the needs of a different population (pregnant women) and setting (Nanjing city) as recommended by the MRC framework [18]. The stages in co-designing the group-based PFMT programme are described in Additional file 2. In brief, the exercise includes three repetitions with 2-min rests between each repetition. One repetition comprised eight contractions with each held for 6 s, followed by three or four fast contractions. Learning and practising the exercise will be supervised in the group sessions and will be required to be repeated twice per day at home between group sessions.

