## Discussion

This study aims to assess the feasibility of implementing a theory-based PFMT programme in a group format with pregnant women. This study will support the design of a definitive RCT with adequate power examining the effectiveness of group-based PFMT in preventing and treating UI in pregnant women. The methods of this study will be modified in a future trial if there are any qualitative or quantitative indicators of problems with acceptability and feasibility that have an impact on recruitment, retention, randomization or fidelity. If there is a significant modification, a pilot study with clear stop/proceed rules will be considered prior to a full trial. The data will not be used to assess the effectiveness of the group-based PFMT programme within this feasibility study.

The strengths of this study include the group-based PFMT programme having been co-designed with stakeholders based on behaviour change theory which will facilitate adherence to the training programme. In addition, this study will investigate the facilitators and potential barriers to participating in and delivering a group-based PFMT programme from both participants’ view and the healthcare provider’s view. A limitation is that there will only be one midwife responsible for delivering group-based PFMT. This may not simulate real clinical practice and lack of experience in delivering group-based PFMT programmes by different health providers. Another limitation is this study only included nulliparous women which may limit the generalizability of the findings in all pregnant women. If a group-based PFMT programme in pregnant women in Nanjing city is shown to be feasible and effective, this will offer support for the future definitive trial.

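### The between-group tests do not return the SD they are said to be run for, leave the baseline score unused, and treat women trained in groups of eight as independent

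*Protocol article*

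**What the plan says.** The section on analysis of quantitative and qualitative data fixes the method: "Group comparisons in UI outcome measures will be analysed using the Mann–Whitney test and chi-square test and presented with confidence intervals". The same sentence gives the aim as "to evaluate evidence of the promise of the intervention". The next sentence says the comparison is "conducted only to obtain standard deviations of quantitative outcome measures of UI and to estimate sample size for the definitive RCT", and not meant to show a definitive difference. The Discussion adds: "The data will not be used to assess the effectiveness of the group-based PFMT programme within this feasibility study".

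The Interventions section describes how the active arm is delivered: "The participants in the intervention group will receive PFMT supervision in groups of eight women". Motivation between sessions is "supported by WeChat groups which will be limited to the eight pregnant women in the group session", and peer support there is encouraged. Under Comparator, control women receive verbal instruction from midwives and no further supervision. Study design schedules assessments at baseline, about 36 weeks and 42 days after delivery. Measures names self-reported UI and the ICIQ-SF as the UI outcomes. Sample size gives 24 women per arm, no SD, and no formal calculation.

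**The concern.** Three features of the named analysis do not fit its stated use.

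- **Method and purpose do not match.** A Mann–Whitney test works on ranks and a chi-square test on counts. Neither produces the SD for which the comparison is said to be run.
- **Independence is assumed.** Twenty-four intervention women make three groups of eight who train and exchange messages together, while controls are treated individually. This is a partially nested design. If group members become alike, which encouraged peer support makes plausible, both tests and the usual intervals understate the uncertainty.
- **The baseline score is unused.** It is collected, but neither named test includes it. Its correlation with follow-up would be a useful input to the definitive design.

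The section also gives two purposes that cannot both be the only one. The Abstract lists a sample size for the future study among the products of this one, so the quantities carried forward matter.

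**Working it through.** **The plan's own figure.** The only N stated is 48 (24 per arm), with no derivation. The cited 10 per arm, inflated for the upper attrition of 53.33%, gives 10/(1 − 0.5333) = 21.4, so 22; rounding up to whole groups of eight gives 24. This is a plausible reconstruction only. No N for the definitive trial is stated.

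**Does the rank test carry an SD?** Two simulated samples of 24 were compared before and after a monotone transform that changed one arm's SD from 4.0 to 12.1. U stayed at 397 and p at 0.025, so the test result does not determine the SD.

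**Can the SD be obtained otherwise?** Yes, descriptively. The 95% limits for a pooled SD are 0.83 to 1.26 times the estimate with 48 evaluable women (46 df), and 0.81 to 1.31 times with 36 (34 df), the progression threshold at the second follow-up.

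**Clustering.** Inputs are group size 8 (Interventions), equal arms (Sample size) and an assumed ICC of 0.02, 0.05 or 0.10; the documents give none. The intervention-arm factor is 1 + (8 − 1)·ICC, the control factor is 1, and the mean over arms is (2 + 7·ICC)/2. Intervals should be wider by the square root of that mean. A trial planned at 90% power, two-sided 5%, without the factor has power Φ(3.2415/√mean − 1.96), where 3.2415 = 1.9600 + 1.2816.

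| ICC | Intervention arm | Mean over arms | Rise in N | Interval wider by | Power |
|---|---|---|---|---|---|
| 0.02 | 1.14 | 1.07 | 7% | 3% | 88.0% |
| 0.05 | 1.35 | 1.175 | 17.5% | 8% | 84.9% |
| 0.10 | 1.70 | 1.35 | 35% | 16% | 79.7% |

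In a simulation of 24 controls against three groups of eight (20,000 runs, nominal 5%), the Mann–Whitney type I error was 4.6%, 6.6%, 8.9% and 12.9% at ICC 0, 0.05, 0.10 and 0.20.

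**Baseline adjustment.** The residual variance is 1 − r². At assumed r of 0.3, 0.5 and 0.7 it is 0.91, 0.75 and 0.51, a reduction of 9%, 25% and 51%.

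**Illustration.** Take a 4-point ICIQ-SF difference (the lower end of the range in Sample size), an assumed SD of 5, and 90% power: n = 2 × 3.2415² × 25/16 = 32.8, so 33 per arm. Clustering alone gives 33 × 1.07 = 35.3 (36), 33 × 1.175 = 38.8 (39) or 33 × 1.35 = 44.6 (45). Baseline adjustment alone gives 33 × 0.91 = 30.0 (31), 33 × 0.75 = 24.8 (25) or 33 × 0.51 = 16.8 (17). If the ICC is taken to apply to the adjusted scores, the joint factor runs from 1.07 × 0.51 = 0.55 to 1.35 × 0.91 = 1.23. The two omissions therefore pull in opposite directions.

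**Can this study estimate the ICC?** Not usefully. With three groups of eight and an F ratio at its expected value for a true ICC of 0.05, the exact 95% interval is about −0.09 to 0.87.

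**The case against.** A reader might infer that the named tests cannot supply a sample size. The documents do not support that. An SD is a descriptive summary of the same scores, and naming a test does not block it. Arm proportions size a trial with a binary outcome without any SD. The Mann–Whitney probability itself gives a sample size through Noether's formula: for P = 0.70 at 90% power, 3.2415²/(12 × 0.25 × 0.20²) = 87.6, so 88 in total. Such an N would be uncorrected, not unobtainable.

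Nor can one say that the definitive trial is wrongly sized. No N, group size or model is stated for it, and leaving out baseline adjustment would make it larger than needed, not invalid.

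Four further objections stand in part.

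- Confidence intervals are promised, so more than p-values is planned, although the effect measure is not named.
- The protocol cites a UI prevalence of 37.8% in pregnancy and excludes women with UI before pregnancy. Many scores may be zero, so a rank test is defensible as a description.
- The ICC range and the full group size are assumptions. With six per group, the mean factors are (2 + 5·ICC)/2 = 1.05, 1.125 and 1.25, and power is about 89%, 86% and 83%.
- Covariates and ICC reporting are commonly left to an analysis plan, and no progression criterion uses these tests.

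What does not fall away is what the article itself states: a method, a purpose that the method does not serve, and a second purpose in conflict with the first.

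**Conclusion.** The point holds in a limited form. The named tests do not return the SD they are said to be run for, do not use the collected baseline score, and ignore the groups of eight in one arm. The needed summaries can still be taken from the data. Intervals, and any N built on them as they stand, would lack a clustering correction worth 7% to 35% of N at an assumed ICC of 0.02 to 0.10 with full groups of eight. They would also forgo a 9% to 51% variance reduction at an assumed correlation of 0.3 to 0.7. The net error has no fixed sign.

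The two stated purposes must be reconciled. The clash with the Discussion is weaker, since promise is not the same as effectiveness, but the Discussion's closing sentence also speaks of the programme being shown to be effective. Feasibility conclusions are untouched; what is at stake is the quality of the numbers handed to the definitive trial.

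**What to change.** Reword the quantitative analysis paragraph so that estimation is the main output.

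- **ICIQ-SF:** report arm-level SDs, the baseline-adjusted mean difference with a 95% interval (bootstrap or robust if scores are heavily zero), the residual SD and the baseline-to-follow-up correlation. The rank test may stay as a secondary description. The recruitment section places baseline data collection both after consent and after randomization; settle which it is, because the adjustment uses that score.
- **UI yes/no:** report arm proportions and the risk difference with an interval. An ordinary interval ignores the groups too, so the next item applies here as well.
- **Groups:** do not rely on an ICC from three groups. Multiply the intervention arm's variance by 1 + (8 − 1)·ICC over a stated assumed or external range. Do this for the definitive sample size (with its own planned group size) and as a sensitivity widening of the feasibility intervals.
- **Purpose:** state one. If it is planning the definitive trial, remove the aim of judging promise.

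The cost is a few sentences and one model, with no change to recruitment or conduct. Intervals become slightly wider, and the planned N may be larger.
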